### 2.12. Outcome

#### 2.12.1. Primary Outcomes Measures (Confirmatory Analyses)

(A)Questionnaires

Impact of the Disease

The FM Impact Questionnaire Revised (FIQR) [28] is a self-administered instrument composed of 21 items. Each item is rated on a 0–10 scale, with higher scores indicating greater disease impact. The questionnaire is structured into three domains: (a) function, (b) overall impact, and (c) symptoms. The total score, obtained by summing the three domains, ranges from 0 to 100, with higher values reflecting a greater overall impact of FM. In this study, the validated Spanish version of the FIQR [29] will be applied.

Health-Related Quality of Life

The EuroQol-5 dimensions 5 levels (EQ-5D-5L) measures health-related quality of life across five domains (mobility, self-care, usual activities, pain/discomfort, and anxiety/depression), each with five response levels. It also includes a visual analog scale ranging from 0 (worst health) to 100 (best health). The instrument has been validated in Spanish populations [30].

(B)Physical Fitness

Handgrip Strength

The Handgrip Strength (HGS) test will be used to assess maximal isometric hand strength. Participants will stand upright with their elbow extended at hip height and exert maximal force on a hand-held dynamometer (Takei TKK 5401, Takei Scientific Instruments Co., Ltd., Tokyo, Japan) featuring analog grip and adjustable handle to accommodate various hand sizes. Two repetitions will be performed for each hand, with a one-min rest interval between attempts. The highest value from each hand will be used for analysis [31].

Timed Up and Go

The Timed Up and Go (TUG) test is a dynamic test of mobility and balance in which participants rise from a chair without using their hands, walk 3 m as quickly as possible without running, turn around a cone, return to the chair, and sit down [32]. Performance is measured as the time taken to complete the task with ChronoJump software (version 2.2.0 Barcelona, Spain) and Chronopic hardware (DIN A-4, 210 × 297 mm), which will be placed on the backrest of the chair; one practice trial will be allowed for familiarization, after which the test will begin with the command “Ready, go”.

Short Physical Performance Battery

The Short Physical Performance Battery (SPPB) evaluates lower-body functional capacity through three components: tasks assessing standing balance, usual gait over 4 m, and the five-repetition sit to stand test [33]. Each component is scored from 0 to 4, with lower scores indicating greater risk of frailty, disability, and falls. The total score ranges from 0 to 12 and is categorized as dependent (0–3), frail (4–6), pre-frail (7–9), and robust (10–12) [33].

30 s Chair Stand Test

The 30 s Chair Stand Test (CTS) will be used to assess lower-limb strength and power. Participants will sit with their arms crossed at chest level, stand to full knee extension, and return to the starting position until the backrest is touched, repeating the cycle as many times as possible in 30 s [34]. Two practice trials will be allowed for familiarization, after which the test will begin with the command “Ready, go”. Performance will be recorded using the ChronoJump software (version 2.2.0, Barcelona, Spain) and Chronopic hardware (DIN A-4, 210 × 297 mm, ChronoJump, Barcelona, Spain), which will be placed on the seat of the chair. Only correctly executed repetitions will be counted. This test has shown good reliability and validity in women with FM [35].

30 s Arm Curl Test

The 30 s Arm Curl (ACT) test will be used to assess upper-limb strength and endurance. Participants will sit in a chair with their feet flat on the floor and their back supported. Grasping a 2.5 kg weight in the dominant hand while maintaining a neutral wrist position, they will perform repeated elbow flexion and extension through the full range of motion for 30 s [34]. Two practice attempts will be allowed for familiarization, after which the test will begin with the command “Ready, go”. The total number of correctly executed repetitions will be recorded. This test has demonstrated good reliability in women with FM.

Agility test

The Agility Challenge for the Elderly (ACE) test will be used to assess performance under fall-threatening, real-life-like motor demands. The ACE consists of a standardized course set on a volleyball court, comprising three domains: stop and go, cutting maneuvers, and spatial orientation, each targeting a specific aspect of agility. Participants will complete four trials per session, interspersed with at least 3 min of rest; the first attempt on each testing day will serve as a familiarization trial. Instructions are to walk as fast as possible without running. Errors in the execution of the spatial orientation task (incorrect order) will be recorded. To avoid learning effects, cone numbers will be individually randomized for each trial. The ACE has demonstrated high reliability and validity in older adults [23].

Dual-Task Condition

Under dual-task conditions, participants will be required to execute a physical task (TUG, ACT, and CST) while concurrently engaging in a cognitive activity. The cognitive task will involve performing serial subtractions by two, starting from a randomly selected odd number greater than 100.

#### 2.12.2. Secondary Outcomes Measures (Exploratory Analyses)

(A)Questionaries

Sociodemographic Information

Participants will report demographic information (level of education and occupation) and clinical information (age, current medications, diagnosed conditions, history of falls, pain level measured by a visual analog scale, injuries, and other relevant health data).

Anthropometric Measurement

Body composition will be assessed using the Tanita Body Composition Analyzer BC-418 MA (Tanita Corp., Tokyo, Japan) along with a SECA 769 column scale and stadiometer (SECA Corp., Hanover, MD, USA).

Physical Activity Level

The International Physical Activity Questionnaire (IPAQ) Short Version will be used to assess physical activity and sitting time. This has been used to calculate total metabolic equivalents (METs) per week and the amount of time spent sitting [36]. The short Spanish version of the IPAQ will be used in this study and has shown strong reliability and validity among in Spanish populations [37].

Fear of Falling

The Fall Efficacy Scale International (FES-I) is a self-report questionnaire consisting of 16 items, with each rated on a four-point scale. The higher the score, the greater the fear of falling. The Spanish version of FES-I will be used [38], which has shown high reliability and validity [39].

Health and Wellbeing

The EQ-Health and Wellbeing (EQ-HWB) will be used to evaluate health and wellbeing in the study population [40]. This generic instrument, developed by the EuroQol Research Foundation, includes a 25-item version that assesses multiple domains such as activity, relationships, cognition, self-identity, autonomy, emotional state, and physical sensations. A shorter version, the EQ-HWB-9 (nine items), will also be administered, focusing on core aspects including mobility, daily activities, loneliness, concentration/clarity of thought, sadness/depression, anxiety, pain, and fatigue. The Spanish versions of the EQ-HWB and EQ-HWB-9 [41], which have demonstrated good validity, will be administered It should be noted that the EQ-HWB and EQ-HWB-S are currently classified as experimental instruments under the Intellectual Property Policy of the EuroQol Research Foundation.

Cognitive Impairment

Montreal Cognitive Assessment (MoCA) is a short screening instrument intended to assess various cognitive domains, such as attention, executive functions, memory, language, visuospatial abilities, calculation, and orientation [42]. In this study, a cut-off score of 23/30 was applied to enhance diagnostic accuracy and minimize false positives [43].

Perceived Exertion

The Borg Rating of Perceived Exertion (Borg-RPE) scale is a tool used to monitor exercise intensity. The original RPE scale ranges from 6 (“no exertion at all”) to 20 (“maximal exertion”) [44]. The modified version, the Borg Category-Ratio 10 scale (Borg-CR10), ranges from 0 (“nothing at all”) to 10 (“extremely strong”) [45]. Both scales have demonstrated high reliability and validity [46]. The Spanish versions of both scales will be administered.

(B)Neurophysiological Variables

Electroencephalography and Heart Rate Variability

Participants will be seated in a quiet room with their feet flat on the floor and eyes open and instructed to remain quiet for five min to acquire baseline resting Electroencephalography (EEG) and Heart Rate Variability (HRV) data. During this procedure, an adhesive electrode (Kendall™ H1224SG, CardinalHealth™, Dublin, OH, USA) will be placed in the left lower thoracic region, below the breast area, over the intercostal space corresponding to the cardiac region, to record cardiac activity. EEG and HRV will be recorded using the Enobio^®^ system instrument (Neuroelectrics, Cambridge, MA, USA) with the NIC2 software, version 2.1.4.1 (for Windows) [47]. This equipment has demonstrated high reliability, even with dry electrodes [48]. EEG activity will be obtained from 19 channels following the international 10–20 system, covering frontal (Fz, Fp1, Fp2, F3, F4, F7, and F8), central (Cz, C3, and C4), temporal (T3, T4, T5, and T6), parietal (Pz, P3, and P4), and occipital (O1 and O2) areas, using the mastoids as references. Impedance will be maintained below 10 kΩ. Signals will be sampled at 500 Hz, applying a 50 Hz notch and a 1–40 Hz bandpass filter. For data processing during movement tasks, recommendations from Cheron et al. [49] will be followed, applying an Artifact Subspace Reconstruction (ASR) filter [50]. Preprocessing and analysis will be performed in EEGlab (v2021, Matlab toolbox; San Diego, CA, USA), where artifacts from ocular, muscular, or electrical sources will be removed using Independent Component Analysis (ICA) [51]. Cleaned data will then be divided into spectral bands: theta (4–7 Hz), alpha-1 (8–10 Hz), alpha-2 (11–12 Hz), beta-1 (13–18 Hz), beta-2 (19–21 Hz), and beta-3 (22–30 Hz) using the pop_spectopo.m function.

HRV signals will be exported in .edf format and analyzed with Kubios HRV software (version 2.1) [52]. The extracted metrics will include: (a) time-domain variables—mean HR, RR, SDNN, Pnn50, and rMSSD; (b) frequency-domain indices—low frequency (LF)/high frequency (HF) ratio (LF/HF) and total power; and (c) nonlinear parameters—approximate (ApEn) and sample entropy (SampEn).

Stimulus–Response Paradigm

Stimulus–Response (S-R) paradigm, a modified version of the methodology proposed by Colzato et al. [53] and Rawish et al. [54], will be employed and adapted to better approximate real-life contexts. Whereas the original studies examined the neural processes involved in file event processing, our approach will incorporate scenarios with greater ecological validity.

Participants will be seated in front of a 15.6-inch (39.6 cm) computer screen, maintaining a viewing distance of approximately 60 cm. The stimulus–response paradigm will be implemented using OpenSesame software, version 4.0.29 (for Windows, OpenSesame Inc., Portland, OR, USA), developed by Sebastiaan Mathôt: https://osdoc.cogsci.nl/4.0/download/ (accessed on 3 September 2024), for the presentation of visual stimuli. The paradigm will follow the sequence described below (see Figure 2):Pre-Cue: A black screen with a white plus symbol (“+”, 64 × 64 pixels) will be displayed for 1500 milliseconds;Cue: A 1500-millisecond video will be shown featuring a woman walking either to the left or right across a pedestrian crossing. The walking direction will be randomized;Pre-S1: An image of a store logo will be presented for 1000 milliseconds;Stimulus S1: A second video (3000 milliseconds) will be shown, in which the same woman will continues walking on the pedestrian crossing and displays an unexpected behavior in response to a balance loss. To recover, she performs a compensatory stepping strategy: either a lateral step or a forward step. A visual distractor (a red or grey car) will also be present in the background;Pre-S2: The same store logo image will be shown again, now for 2000 milliseconds;Stimulus S2: A second instance of the stimulus will be presented, with the same characteristics as S1 but randomized.

The paradigm will include two conditions related to feature overlap between S1 and S2:Complete feature overlap (S1 = S2): Same stepping strategy and same car color;No feature overlap (S1 ≠ S2): Different strategy and different car color.

During each trial (S1 and S2), participants will provide two responses (R1 and R2) by pressing either the left or right control key with their index fingers.

R1: Participants will memorize the walking direction shown in the Cue phase (left or right) and respond with the corresponding key when S1 appears;R2: Participants will quickly indicate the stepping strategy shown in S2: the left key for a forward step and the right key for a lateral step.

This task structure will allow for the identification of four conditions based on response and feature overlap:(a)Stimulus feature overlap with response repetition (S1 = S2 and R1 = R2);(b)Stimulus feature overlap with response alternation (S1 = S2 and R1 ≠ R2);(c)No stimulus feature overlap with response repetition (S1 ≠ S2 and R1 = R2);(d)No stimulus feature overlap with response alternation (S1 ≠ S2 and R1 ≠ R2).

The full task consists of 80 trials, distributed across five blocks of 40 trials each. Reaction times and response accuracy will be recorded throughout the experiment. Prior to the actual task, participants will complete a 5-min practice session without wearing the EEG recording cap.

During this test, EEG and HRV will be recorded. To achieve this, the Enobio^®^ instrument (Neuroelectrics, Cambridge, MA, USA) and the OpenSesame software, version 4.0.29 (for Windows, OpenSesame Inc., Portland, OR, USA)will be synchronized using the Lab Streaming Layer (LSL). EEG time–frequency analysis will be performed specifically within this paradigm to examine neural dynamics associated with the different task events. EEG data will be epoched relative to the onset of S2 (0 ms) and segmented according to task phases (Figure 3): Pre-Cue (−9000 to −7500 ms), Pre-S1 (−6000 to −5000 ms), S1 (−5000 to −2000 ms), Pre-S2 (−2000 to 0 ms), and the within-trial interval (0 to 1000 ms). Time–frequency decomposition will be conducted using Morlet wavelets (width = 5 cycles) with a Hanning taper. For each electrode and time point, the average spectral power will be computed within the theta (4–7 Hz), alpha (8–12 Hz), and beta (12–30 Hz) frequency bands. Comparisons will be performed between stepping strategies (lateral vs. forward) and task load (single-task vs. dual-task), with pointwise *t*-tests calculated for each time point in the 0–1000 ms window after S2 onset. False-Discovery Rate (FDR) correction will be applied to account for multiple comparisons, and effect sizes (r) will be reported for significant differences.

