**Figure 3 sports-14-00059-f003:**
[figure not shown]
Graphical representation of a single trial within the stimulus–response (S-R) paradigm adapted from Colzato et al. [53]. The temporal structure of the task is illustrated along a timeline. The pre-cue phase corresponds to the interval preceding cue presentation (from −9000 to −7500 ms relative to S2). The pre-S1 phase spans from to 6000 to 5000 ms, followed by the post-S1, which extends from 5000 to 2000 ms before the onset of S2. The pre-S2 interval covers the 2000 ms immediately preceding S2 (prone), whereas the post-S2 interval corresponding to the within-trial phase includes the 1000 ms following probe onset. Participants will be instructed to memorize the direction indicated by the cue. When stimulus S1 appears, they will respond by indicating the cue direction using the left or right control key. Upon presentation of S2, participants will identify the required movement, selecting the right control key for unloaded sidesteps and the left control key for a single forward step.

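### Each S2 stepping strategy has its own fixed response key, so the exploratory lateral-versus-forward EEG contrast after S2 cannot be separated from right- versus left-hand responding

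*Protocol article*

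**What the plan says.** The Stimulus–Response Paradigm text in section 2.12.2 asks for two key presses per trial, made by "pressing either the left or right control key with their index fingers". The first, R1, is given when S1 appears and reports the walking direction from the cue. The second, R2, concerns S2: "Participants will quickly indicate the stepping strategy shown in S2", with "the left key for a forward step and the right key for a lateral step". The Figure 3 legend states the same rule: "selecting the right control key for unloaded sidesteps and the left control key for a single forward step". The article says which task features are randomized (walking direction and the characteristics of S2), but describes no reversal or counterbalancing of the R2 keys.

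For the analysis, at each electrode "the average spectral power will be computed within the theta (4–7 Hz), alpha (8–12 Hz), and beta (12–30 Hz) frequency bands". The planned tests are then set out: "Comparisons will be performed between stepping strategies (lateral vs. forward) and task load (single-task vs. dual-task"), using "pointwise *t*-tests calculated for each time point in the 0–1000 ms window after S2 onset", with FDR correction. Responding hand is not a factor in this comparison. Section 2.13 classes the EEG measures as secondary and exploratory.

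**The concern.** The contrast is meant to show whether the brain responds differently to a lateral and a forward compensatory step. Its window opens at the stimulus that demands a quick key press, and the step shown decides which key is pressed. With one index finger per control key, the natural reading is that forward means left hand and lateral means right hand, for every woman at both visits. Left- and right-hand responses are expected to differ in alpha and beta power over the motor areas, and C3 and C4 are among the 19 recorded channels. A lateral-minus-forward difference there could appear with no step effect at all, and a true step effect could be hidden by an opposing hand effect. The purpose given for these analyses is mechanistic insight, and a contrast that cannot tell the two sources apart offers little of it.

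**Working it through.** The plan gives no figure to reproduce here. The check is whether the design allows the step effect to be estimated apart from the hand effect.

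**Inputs, all from section 2.12.2.** R1 follows cue direction. R2 follows the S2 step by the fixed rule. S1 and S2 either overlap fully (same step, same car color) or not at all.

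**Timing.** The phases before S2 add up to 1500 + 1500 + 1000 + 3000 + 2000 = 9000 ms, which agrees with the stated epoch start at −9000 ms. Zero is therefore the onset of the stimulus that calls for R2.

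**Enumeration.** Cue direction (2) × S1 step (2) × overlap (2) gives 8 trial types. With correct responses:

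| Pair | Correlation |
|---|---|
| S2 step and R2 hand | 1.0 |
| S1 step and R1 hand | 0.0 |
| S2 step and R1 hand | 0.0 |

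The matrix [intercept, S2 step, R2 hand] has rank 2 of 3, so step and hand effects in the post-S2 window are not separately estimable.

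**What the contrast estimates.** Code step x and hand h as −½ (forward, left) and +½ (lateral, right), and write power as μ + τx + ηh.

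- Fixed mapping, correct trials: h = x, so lateral minus forward = τ + η.
- Error trials included, accuracy a: the correlation is 2a − 1 and the contrast is τ + (2a − 1)η. The documents give no accuracy. At assumed values of 95%, 90% and 80%, the share of the hand effect left in the contrast is 0.90, 0.80 and 0.60. Only wrong responses break the tie.
- Reversed mapping, correct trials: h = −x, so the contrast is τ − η.
- Equal average of the two mappings: ½[(τ + η) + (τ − η)] = τ. The step–hand correlation falls to 0.0 and the matrix has rank 3 of 3.

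**Multiplicity correction.** FDR limits the proportion of rejections that are chance findings. If η ≠ 0, the tested difference is truly nonzero even when τ = 0, so the correction does not protect against this misreading.

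**Group-by-time comparison.** If η is the same in both arms and at both visits, it drops out: [(τ + η) post − pre in exercise] − [the same in control] contains no η.

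**The case against.** Four points on the other side carry weight.

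1. **S1 supplies some separating information.** A reader might infer that every lateral step in the task is answered with the right hand and that no analysis could ever help. The documents do not support this. At S1 the key follows the randomized cue direction, so lateral steps there are answered with either hand, and the plan already segments the S1 phase. That help is indirect: R1 can be prepared before S1 appears, the step is not the response feature at S1, and carrying a hand effect from S1 to S2 needs an additivity assumption.
2. **The timing is not documented.** If S2 runs like the 3000 ms S1 video, the step may become visible late. The article gives neither that moment nor an expected reaction time. Hand selection could fall partly or wholly outside the first 1000 ms, so the degree of contamination is unknown. The collinearity in the planned test is not.
3. **The size cannot be derived.** One might attach a false-positive probability to the contrast. That would need an assumed hand effect and, in its simple form, uncorrected testing in the full sample, whereas the plan applies FDR and section 4.3 refers to an EEG subsample of unstated size.
4. **The reach is narrow.** A reader might extend the point to reaction time and accuracy by strategy, or to the EEG results generally. The article only says that reaction time and accuracy are recorded, and the Discussion anticipates improvement in them; no comparison by strategy is planned. The EEG objective and hypothesis concern resting-state activity.

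These limit the scope and the certainty about size. They do not remove the confound from the stated test.

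**Conclusion.** The point holds for S2 and for the lateral-versus-forward power contrast in the first 1000 ms after it. On correct trials step type and responding hand coincide completely (correlation 1.0, rank 2 of 3), so the contrast returns τ + η and cannot be read as step processing alone. The worry is greatest for alpha and beta at C3/C4, and applies to the extent that hand selection falls inside the window.

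Two assumptions underlie this: that each control key is pressed by the hand on its own side, and that hand preparation or execution affects power in the window. The first is the natural reading of the text. The second is not quantified in the documents, so no numerical bias is claimed.

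The consequence is an ambiguous exploratory finding, not a compromised trial. Resting EEG, the task-load contrast and the primary outcomes are unaffected, and a hand effect common to arms and visits would cancel in a group-by-time comparison.

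**What to change.** Counterbalance the R2 mapping. Within each association, assign half the women (as nearly as numbers allow) forward = left key and lateral = right key, and the other half the reverse. Keep each woman's mapping the same before and after the intervention. Estimate the lateral-versus-forward contrast as the equally weighted average over the two mappings, or include mapping as a factor. Revise the R2 rule in section 2.12.2 and the Figure 3 legend to match.

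The cost is one participant-level variable in the OpenSesame script and one more analysis factor, with no extra visits or recordings. The downside is some added between-person variance from mapping. The change has to be made before the first baseline recording, since a woman's mapping should not switch between visits.

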### 2.3. Randomization of Assessments

The assessments will follow a fixed sequence with alternating tests of the upper and lower limbs, thereby ensuring adequate rest periods to prevent cumulative fatigue and optimizing the overall time required for the evaluations. To reduce familiarization and learning effects, the sequence of specific conditions will be randomized. Randomization will apply to both the physical test conditions and the arithmetic cognitive task.

The physical tasks that each participant will complete at baseline (pre) and post-intervention will be scheduled across two assessment days:Day 1: Cognitive task (arithmetic-based counting test), handgrip strength, timed up and go test (TUG), arm curl test (ACT), and 30 s chair stand test (CST). Randomization: The random allocation sequence will be generated by an independent researcher using a computer-based random number generator (Random Number Generator tool; Google, LLC., Mountain View, CA, USA) and implemented via a password-protected Excel file. Simple randomization (0/1) will be used for Day 1 tasks. Personnel responsible for enrolling participants and conducting assessments will remain blinded to the random allocation sequence. Two aspects will be randomized for each participant: (1) whether the arithmetic subtraction task is performed at the beginning (coded as 1) or at the end (coded as 0) of the physical test sequence and (2) whether the motor task is performed as a single-task condition (coded as 0) or as a dual-task combined with the cognitive subtraction task (coded as 1). The handgrip test will be performed without dual-task condition due to its temporal execution characteristics;Day 2: Baseline resting Electroencephalography (EEG) and Heart Rate Variability (HRV), EEG and HRV combined with the Stimulus–Response (S-R) paradigm protocol, Short Physical Performance Battery (SPPB), and Agility Challenge for the Elderly (ACE). Randomization: Only the spatial orientation component of the ACE test will be randomized according to the recommendations of Lichtenstein et al. [23]. The random allocation sequence for this task will also be generated by the independent researcher, recorded in the same password-protected Excel file, and accessed by the researcher immediately prior to testing to ensure allocation concealment

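### The stimulus–response EEG task is given as 80 trials in five blocks of 40 (which is 200), and one of its two planned contrasts uses a dual-task level that the task does not have

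*Protocol article*

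**What the plan says.** All of the following is in the protocol article.

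- **Task length** (2.12.2, Stimulus–Response Paradigm): "The full task consists of 80 trials, distributed across five blocks of 40 trials each". A 5-minute practice session comes before the task and is described separately.
- **Setting** (same section): "Participants will be seated in front of a 15.6-inch (39.6 cm) computer screen". Responses are left or right key presses. Only one version of the task is described.
- **Conditions** (same section): "This task structure will allow for the identification of four conditions based on response and feature overlap". The four are stimulus overlap or none, crossed with response repetition or alternation.
- **Planned EEG tests** (same section): "Comparisons will be performed between stepping strategies (lateral vs. forward) and task load (single-task vs. dual-task), with pointwise *t*-tests calculated for each time point". These tests cover the first second after S2. On multiplicity: "False-Discovery Rate (FDR) correction will be applied to account for multiple comparisons".
- **Meaning of dual task** (2.12.1, Dual-Task Condition): "participants will be required to execute a physical task (TUG, ACT, and CST) while concurrently engaging in a cognitive activity". The cognitive activity is serial subtraction.
- **Scheduling** (2.3): TUG, ACT and CST are on Day 1. EEG and the stimulus–response task are on Day 2, where "Only the spatial orientation component of the ACE test will be randomized".
- **General analysis** (2.13): a mixed model with group, time and their interaction, without a list of outcomes, and a 2 × 2 analysis of EEG before and after the intervention in alpha and theta. The text does not name the two factors or say whether resting or task EEG is meant.

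**The concern.** Two statements in the methods text cannot be carried out as written.

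First, the trial count and the block structure disagree. The number of trials is fixed when the data are collected, so an error here cannot be repaired at analysis. It sets the averaging noise in each condition and the length of the session, in a population for whom the Introduction lists fatigue as characteristic, and SPPB and ACE follow the task on the same day.

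Second, one of the two EEG contrasts compares levels of a factor that the task does not vary. Meanwhile the four conditions that the task does create appear in neither contrast. The Discussion frames the task around forming and retrieving event files and anticipates higher theta, alpha and beta power during it after the intervention. The tests tied specifically to this paradigm do not address that expectation.

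**Working it through.** **1. Trial count**

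Inputs from 2.12.2: total 80, blocks 5, trials per block 40.

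- Blocks × trials per block = 5 × 40 = 200, not 80. The ratio is 200 / 80 = 2.5.
- Keeping 80 in total and five blocks gives 80 / 5 = 16 per block.
- Keeping 80 in total and 40 per block gives 80 / 40 = 2 blocks.
- Treating one block as practice gives 4 × 40 = 160. Counting two responses per trial, or two visits, gives 80 × 2 = 160. Neither turns 80 into 200, or five blocks of 40 into 80.

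No reading reconciles the three numbers. At least one is wrong, and the article does not show which.

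**2. What the discrepancy amounts to**

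Phase durations to S2 onset, from 2.12.2: 1500 + 1500 + 1000 + 3000 + 2000 = 9000 ms. This agrees with the stated epoch start of −9000 ms, so the trial timeline itself is consistent.

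| | 80 trials | 200 trials |
|---|---|---|
| Per condition, if the four are balanced | 80 / 4 = 20 | 200 / 4 = 50 |
| Minimum time, 9 s per trial | 80 × 9 / 60 = 12 min | 200 × 9 / 60 = 30 min |
| Time if S2 lasts 3 s like S1 (assumed), 12 s per trial | 80 × 12 / 60 = 16 min | 200 × 12 / 60 = 40 min |

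The trial-averaging part of the standard error of one participant's condition mean differs by √(50 / 20) = √2.5 = 1.58. Variation between participants does not shrink with more trials, so the effect on a comparison of groups is smaller than this.

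**3. The task-load contrast**

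| Needed for the contrast | What the article provides |
|---|---|
| A single-task and a dual-task version of the task | One seated key-press task; its factors are feature overlap and response repetition (2.12.2) |
| A dual-task condition with EEG | Dual task covers TUG, ACT and CST only (2.12.1), on Day 1; EEG is listed only on Day 2 (2.3) |
| Assignment or ordering of load on Day 2 | Only the ACE spatial orientation component is randomized (2.3) |
| An S2 onset to define the 0–1000 ms window | Exists only in the stimulus–response task |

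As described, the single-task versus dual-task contrast has no data.

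**4. What the planned contrasts leave out**

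The two contrasts in 2.12.2 are stepping strategy and task load. Neither is overlap × repetition, and neither involves group or visit. The general model in 2.13 has group × time but no outcome list. The pre/post EEG analysis there names alpha and theta only, whereas the Discussion also expects a beta change during this task.

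**The case against.** The strongest reply is that this is an exploratory measure in a condensed article. Objective (b) and H2 concern resting-state EEG and HRV, and section 2.13 says that the EEG analyses are not confirmatory. The trial count would normally be programmed once in the presentation software, so the sentence may be a reporting slip. Which condition contrasts are tested could be left to an analysis plan.

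Much of this stands, and it limits the point. It does not remove the two contradictions. A sentence whose numbers disagree, and a contrast on a factor absent from the task, are errors in what is stated rather than detail left out.

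A reader might go further in three ways that the article does not support:

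- *That groups or visits are never compared on this EEG.* Section 2.13 plans a general group × time model and a pre/post EEG analysis, and neither excludes the task data. What can be said is that 2.12.2 states no such contrast and 2.13 does not say whether it covers this EEG.
- *That associations or visits would run different task lengths, confounding the comparison.* Nothing in the article suggests this.
- *That the task-load contrast must be a mistake.* Section 2.12.2 mentions EEG processing for movement tasks, so the authors may have a version in mind that they have not described. The text supports removing or defining the contrast, not assuming which is intended.

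**Conclusion.** The concern holds for the two contradictions. Five blocks of 40 is 200 trials, not 80, and the single-task versus dual-task EEG contrast has no matching level in the task described.

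The size of the first is a factor of 2.5: 20 versus 50 trials per condition, and at least 12 versus 30 minutes. The per-condition figures assume balance, which the article does not state. The minimum times count only the phases up to S2 onset and leave out S2 itself and any breaks. The second means that one of the two contrasts planned for this EEG cannot be computed.

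The missing overlap × repetition contrast, and the unclear reach of the models in 2.13, are a weaker and related point: the intended comparison should be named when the invalid one is corrected. Because the outcome is secondary and exploratory, the primary outcomes, the sample size and the confirmatory analyses are not affected. This should be corrected, ideally before data collection, because the trial count cannot be changed afterwards.

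**What to change.** In 2.12.2:

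1. State one consistent trial and block count: 5 × 16 = 80, 2 × 40 = 80, or 5 × 40 = 200. Say that it is the same at both visits and in all associations. The authors should confirm it against the programmed task.
2. Remove the task-load contrast, or describe the version of the task that supplies a dual-task level and when it is recorded.
3. In its place, name the overlap × repetition contrast on which the task is built. Whether it is tested time point by time point or on a window average is the authors' choice.
4. State that the pre/post change in this contrast is compared between groups under the group × time model of section 2.13, and in which bands. Say also whether the 2 × 2 EEG analysis in 2.13 refers to resting or task recordings.

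The cost is a few sentences and an analysis script. No new measurements are needed, unless the authors choose to keep the task-load contrast and must add a dual-task version.
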